#### Participant withdrawal

All participants will receive written and verbal information about their opportunity to withdraw from the study at any time without any consequences, and in that event, the participant’s data will be deleted. Participant withdrawal is possible under specification of the participant’s code number. A withdrawal of anonymized data is not possible.

### Baseline data

The following data will be surveyed from breast care centers before randomization: Primary cases of DCIS treated with (1) breast-conserving therapy, (2) additional recommendation of radiotherapy afterwards and (3) mastectomy in 2014, certification body (Onkozert, EUSOMA, ÄKzert), number of specialized nurses in the breast care centers, number of treating physicians and procedures in the breast care center.

Baseline characteristics of specialized nurses include age, gender, working experience, training and education, job specification, knowledge about DCIS, experiences in patient counselling, participation in physician consultations and tumor boards and nurses’ understanding of their role.

Baseline characteristics of physicians include age, gender, working experience in senology, qualification, attitude towards the inter-professional collaboration and knowledge about evidence-based medicine and SDM.

Baseline characteristics of women with DCIS include age, educational level, disease and diagnostic parameters (size of DCIS, histologic type = grading, architecture, focality, hormone-/HER2-receptor-status if available, comorbidities, mode of detection) (all diagnostic parameters will be extracted from the patient record), information about health information behavior, and advance information about DCIS.

All baseline characteristics except for the women will be assessed before randomization to avoid bias.

### Outcomes

#### Primary outcome: MAPPIN-O_dyad_

Different outcomes have been discussed. For the evaluation of our main hypothesis, we will use the observer instrument “Multifocal APProach to the sharing IN Shared Decision-making” (MAPPIN’SDM) [23]. As an instrument for the assessment of the primary outcome the observer-based instrument MAPPIN-O_dyad_ of the MAPPIN-inventory will be applied. It assesses the mutual SDM behavior of physicians and patients based on video recordings.

Informed choice would have been a suitable endpoint, too. The intervention addresses the enhancement of patient participation, which is part of SDM. The estimation of patient participation requires an analysis of the decision-making process and its communicative details. Informed choice is an outcome measure, which correlates with patient participation, but it is not congruent. Therefore, the process itself is the primary endpoint of the study, and further outcome variables have been defined as secondary endpoints. A list of all outcomes is provided in Table 1.

**Table 1 Tab1:**
[figure not shown]
Outcome parameters

MAPPIN-O_dyad_ is one part of the MAPPIN’SDM inventory that enables the appraisal of medical decision communication with three perspectives: physician, patient and observer. The aim of the instrument is to assess the extent of patient participation. All three perspectives consist of the same SDM criteria contained in analogous items. The relevant evaluation unit is the dyad of physician and patient. Physician and patient assess how they perceived the mutual SDM process. The observer rates the SDM behavior of the physician and patient and of the interaction of the dyad (physician and patient) based on video recordings.

The multifocal approach with dyad as evaluation unit is unique for SDM process assessment inventories. Other instruments either skip at least one perspective (for example, SDM-Q) [65, 66] or focus the action of only one conversational partner, mostly the physician (for example, dyadic OPTION, OPTION 5) [67–69]. In fact, a triangular measurement of SDM including the whole decision-making process and all participants (physician, nurse and patient) would be desirable. However, such instruments do not exist [46]. Originally, MAPPIN’SDM has been developed to assess the communication between physician and patient. Meanwhile an adapted version for the decision talk between health care professionals and patients has been published [70]. Therefore the observer-based MAPPIN’SDM-inventory (MAPPIN-O_dyad_) considering the interaction of the patient with both, the physician and the nurse, will give a holistic view of the SDM process (see below). The decision-making process in the IG comprises the decision coaching by the nurse and the patient-physician consultations. In the control group (CG), the decision-making process comprises the patient-physician consultations.

The revised version of the instrument (MAPPIN’SDM_revised_) is available, comprising a set of nine SDM indicators per perspective, which cover the international consensus of the essential SDM competencies [71].

Both MAPPIN’SDM questionnaires (healthcare provider and patient) and the observer instrument comprise 11 items (one indicator has three components). Six indicators outline the chronological order of an SDM talk. Three indicators contain meta-communicative components. All indicators are assessed on a five-point-scale from 0 to 4 (for example, observer instrument: ‘competence was not observed’ to ‘excellent performance’).

For the primary outcome in the IG, two trained raters will independently rate MAPPIN’SDM_dyad_ for the whole decision-making process, consisting of two talks (nurse-patient and physician-patient). In a second step, they build a consensus. In the last step, we will calculate mean values of the final scores for the primary endpoint.

In the CG, the decision-making process is limited to the patient-physician consultations. The rating procedure is identical to the IG, but the decision-making process comprises only one consultation (physician-patient).

Test quality of an observer-instrument consists of several data. The typical item parameters as well as the reliability of the questionnaire are adequate (mean item difficulty = 1.51 (SD = 0.76), mean corrected item total correlation = 0.53 (SD = 0.19), Cronbachs alpha = 0.84). The reliability and validity of the observer data are relevant as well. Previous research has shown adequate interrater-reliability (mean T = 0.45). Validity calculations were conducted by sensitivity and specificity measurement in comparison to one SDM-expert. High validity values were reached (mean sensitivity = 0.67, mean specificity = 0.81) [72].

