#### Control cluster

In the control cluster, standard care will be delivered. Women will not receive any additional information or counselling on treatment options other than that usually provided by breast care centers. In general, standard care comprises one or two physician encounters in which the women are informed about their diagnosis and the treatment recommendation of the tumor board and their informed consent for treatment is obtained. Standard care procedures of each breast care center will be assessed at the beginning of the study. We expect centers to be comparable due to certification guidelines.

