One further limitation is that some breast care centers already involve specialized nurses in counselling of women prior to the treatment decision. Because we only focus on the physician consultation in the control group, we might overlook the SDM behavior of nurses that would lead to an improvement of the extent of SDM in the control group. We will record if nurses are part of the usual counselling process prior to randomization, but the extent and quality of possible nurse counselling regarding SDM will not be quantified. Within the scope of process evaluation, we video tape these nurse encounters, too.

The video recordings might influence healthcare professionals due to the artificial situation. However, this effect might occur in both groups.

The cluster design has been chosen to avoid contamination between study arms. However, breast care nurses are organized in networks and might exchange information about the study intervention.

We defined seeking a second opinion as exclusion criterion. Women might have already been included in the study in the center they visited first and should not be asked for participation a second time.

In summary, the results will indicate if decision coaches will improve informed shared decision-making in oncology and which resources and conditions are necessary to implement the new model in certified breast care centers in Germany.

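### The primary score rates nurse plus physician talk in the intervention arm but one physician consultation in the control arm, so control talks on the same decision may go uncounted

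*Protocol article*

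**What the plan says.** All references are to the Protocol article.

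- **Primary outcome, intervention arm.** Two raters score the dyad "for the whole decision-making process, consisting of two talks (nurse-patient and physician-patient", and then reach a consensus.
- **Primary outcome, control arm.** The text first says: "In the CG, the decision-making process is limited to the patient-physician consultations". The next sentence reads: "The rating procedure is identical to the IG, but the decision-making process comprises only one consultation (physician-patient". The description of the instrument in the same section also uses the plural: "In the control group (CG), the decision-making process comprises the patient-physician consultations".
- **Control cluster.** "In general, standard care comprises one or two physician encounters in which the women are informed about their diagnosis" and the tumor board's recommendation, and in which consent to treatment is obtained.
- **Discussion, further limitations.** Some centers already use specialized nurses for counselling before the treatment decision. The authors write: "Because we only focus on the physician consultation in the control group, we might overlook the SDM behavior of nurses", and add that this behavior would have improved the control arm's SDM. Nurse involvement is noted before randomization, but its extent and quality regarding SDM are not quantified. Even so: "Within the scope of process evaluation, we video tape these nurse encounters, too".
- **Encounters one and two.** All encounters are to be video recorded.
- **Discussion, primary endpoint.** The authors accept that two talks may score higher than one and that systematic differences are possible. Their answer is a holistic measurement of the process in the intervention arm.

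**The concern.** The protocol chooses the process itself as its primary endpoint. A process measure compares the arms fairly only if the same kinds of contact count in both. As written, a control woman counselled by a breast care nurse, or seen twice by physicians, can be scored on part of her process, while a woman in the intervention arm is scored on nurse and physician contact together.

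The lowest item rating means that the competence was not observed. A competence shown only in an unrated control talk therefore earns nothing. For nurse counselling the protocol itself gives the direction: control SDM is understated. The shortfall would be largest in control centers with the most developed usual care. A positive result could then partly reflect which talks were rated rather than what coaching achieved.

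**Working it through.** **1. The rating scope, side by side.**

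| Contact on the treatment decision | Intervention arm | Control arm |
|---|---|---|
| Nurse talk | Rated | Exists in some centers, filmed, not rated |
| Physician talk | Rated | One rated |
| Second physician talk | Not addressed; consultations are plural in the instrument description | Possible under standard care; the plural wording would include it, the one-consultation wording would not |
| Additional coaching session | Allowed under Interventions, Patients; the rating rule names two talks only | Not applicable |

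The nurse row is a stated omission. The second-physician row is an inconsistency: the text does not settle whether that talk is rated or, if only one is, which one. The last row shows that the scope is loosely fixed in the intervention arm too.

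**2. The planned sample size (Sample size section).** Inputs: difference 0.25, SD 0.4, power 90%, two-sided alpha 0.05, ICC 0.02, 12 patients per center.

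- Individually randomized n per arm: 2 × [0.4 × (1.960 + 1.282) / 0.25]² = 53.8.
- Design effect: 1 + (12 − 1) × 0.02 = 1.22.
- Inflated: 53.8 × 1.22 = 65.6 per arm, or 65.6 / 12 = 5.47 centers per arm.
- With a t-test on 2(k − 1) degrees of freedom, k = 6 centers per arm gives 86.3% power and k = 7 gives 91.9%.

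So k = 7, which is 14 centers and 168 patients as stated, or 16 and 192 with the drop-out allowance. The point does not depend on this figure, and the fix leaves it unchanged.

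**3. How sensitive the test is.** The standard error of the difference is 0.4 × √(2 × 1.22 / 12k): 0.068 at k = 7 and 0.064 at k = 8. Suppose the arms do not truly differ in SDM over the whole process, but omitted talks lower the control mean by b. The noncentral t distribution then gives these rejection rates:

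| Assumed b | 168 patients | 192 patients |
|---|---|---|
| 0 | 5% | 5% |
| 0.05 | 10% | 11% |
| 0.10 | 27% | 31% |

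**4. What b would require.** b is the share of control women affected times the mean score lost per affected woman. The protocol gives neither. A b of 0.05 needs, for example, half of control women losing 0.10 each or a quarter losing 0.20. A b of 0.10 needs half losing 0.20 or a quarter losing 0.40, which is a full SD. If no control woman has a further talk, b is zero.

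**The case against.** **Two talks against one is not bias.** This stands. Coaching is the intervention, and an endpoint that ignored it would miss the program's main component. The point concerns only control talks that belong to the same process and are left out.

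**The one-consultation sentence may be shorthand.** It follows a sentence in the plural and contrasts with nurse-plus-physician, so it may count types of talk. A reader might infer that second control physician talks will be filmed and then discarded. The text does not establish that. Control data collection is built around one physician encounter (questionnaires once, afterwards), and the encounter is interrupted for study entry, so an earlier talk may fall outside the filmed period. What remains is an inconsistency in the definition of the primary outcome.

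**The limitation is disclosed and partly mitigated.** Nurse involvement is recorded before randomization. The physician-encounter MAPPIN-O_dyad is reported separately (Secondary outcomes), and separate sub-analyses by type of encounter are planned (Statistical methods). This lets a reader compare physician talk with physician talk, but it answers a narrower question and leaves the primary score as it is. The holistic rating offered as the answer acts on the intervention arm only.

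**The size is unknown.** This also stands. A reader might size the bias by treating the process score as the better of two equally good talks. The protocol instead describes one holistic consensus rating. It also reports that usual care mostly conveys the tumor board's recommendation, so a second such talk might add little. No figure of that kind is supported.

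**Conclusion.** The point holds in limited form. The primary outcome's rating scope differs between the arms, is described inconsistently for the control arm, and leaves out usual-care nurse counselling that the protocol expects in some centers and plans to film. The comparison may therefore favour the program among control women with nurse counselling or a second physician talk. For nurse counselling the authors concede the direction; for a second physician talk it is an inference from the scoring scale.

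That the primary result is biased by a known or large amount does not follow. The share of women affected and the loss per woman are not given. The rejection rates of about 10–30% rest on an assumed b of 0.05 to 0.10 and show only that the design is sensitive to a shift well below the target difference of 0.25. The raters' lack of blinding is a separate, disclosed limitation and is not part of this point.

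**What to change.** Reconcile the Control cluster section with the control-arm wording under Primary outcome, and state one rating unit for both arms. Suggested text:

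> In both arms the rating unit is the complete set of recorded physician and nurse encounters on the treatment decision within the study period, up to and including the final encounter. It is rated once, as a whole, by the same two raters with consensus. In the control arm this includes usual-care nurse counselling and any second physician encounter; in the intervention arm it includes additional coaching sessions.

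In addition:

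- Compare the physician-encounter-only MAPPIN-O_dyad, already reported separately, between the arms as a sensitivity analysis.
- Report the number of rated talks per woman by arm, so that the share of control women with further talks becomes visible.

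**Cost.** Extra rating hours for control women with more than one filmed talk. No new recordings should be needed if encounters are filmed as the protocol says. The expected difference may be somewhat smaller. The Discussion notes that MAPPIN is not validated for processes of two talks; the fix extends that use to the control arm, but the intervention arm already depends on it. The change should be made before rating begins.

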#### Secondary outcomes

##### MAPPIN-Q_(patient/nurse/physician)_

To take patients’ and health care professionals’ perspective of SDM into account, the remaining components of the MAPPIN’SDM-inventory will be used. This comprises women-, nurse- and physician-based judgments about their perceptions of the mutual decision-making process (MAPPIN-Q_patient_, MAPPIN-Q_nurse_ and MAPPIN-Q_physician_, respectively). The healthcare professionals will be familiar with the questionnaire because they fill in the questionnaire for every woman. Patients in the IG fill in the questionnaire two times (talk with nurse, talk with physician), and patients in the CG fill in the questionnaire once.

The concordance between SDM judgment of patient and physician/nurse by a nonparametric concordance measure will be calculated (weighted T (MAPPIN-Q_patient_ and MAPPIN-Q_physician_) and weighted T (MAPPIN-Q_patient_ and MAPPIN-Q_nurse_)).

MAPPIN-O_dyad_ of the decision coaching sessions and MAPPIN-O_dyad_ of the physician encounter will be reported separately, as well as the observer ratings of patients and healthcare professionals (MAPPIN-O_patient_, MAPPIN-O_nurse_ and MAPPIN-O_physician_).

Every part of the MAPPIN’SDM-inventory has 11 items and answer format of a graduated Likert scale from 0 to 4 (see primary outcome). The test values per person are calculated by the mean of the 11 item answers. All MAPPIN’SDM-ratings and -questionnaires that are applied for secondary outcomes have similar test quality as the primary outcome [73].

##### Informed choice

Following up Marteau’s definition of informed choice, the measure of this construct combines three dichotomous dimensions: (a) risk knowledge, (b) attitude and (c) uptake [37]. These three dimensions will be connected to one dichotomous outcome. Informed choice can be obtained if women have adequate risk knowledge of the treatment options, and their uptake of one treatment option is congruent with their positive attitude for the chosen option (see Table 2) [37].

**Table 2 Tab2:** Classifying choices based on the three dimensions of informed choice

Uptake	Good knowledge	Positive attitude toward the option	The choice is
Mastectomy	✓	✓	Informed
	✕	✓	Uninformed
	✓	✕	Uninformed
	✕	✕	Uninformed
Breast-conserving surgery without radiotherapy	✓	✓	Informed
	✕	✓	Uninformed
	✓	✕	Uninformed
	✕	✕	Uninformed
Breast-conserving therapy and radiotherapy	✓	✓	Informed
	✕	✓	Uninformed
	✓	✕	Uninformed
	✕	✕	Uninformed
Watchful waiting	✓	✓	Informed
	✕	✓	Uninformed
	✓	✕	Uninformed
	✕	✕	Uninformed

The single dimensions of the instrument are described below:Risk knowledgeA 12-item knowledge test has been developed to measure risk knowledge. The test includes questions on diagnosis and prognosis of DCIS and benefits and harms of available treatment options in multiple-choice format. It was pretested in the pilot trial. However, it cannot be considered a validated scale. The score is calculated by the sum of correct answers (maximum value 12). Total values will be dichotomized in adequate risk knowledge (at least 75 %; ≥ 8 correct answers) and non-adequate knowledge (<8 correct answers). If patients fill in at least one item of the risk knowledge test, unanswered questions will be rated as incorrect. If none of the questions is answered, the test will be classified as missing data. All patients will fill in the risk knowledge test after their last physician encounter to avoid questions from patients triggered from the test items.AttitudeThe attitude of patients toward the options will be assessed during the SDM process. Because the decision can be influenced by several factors, the attitude in the IG will be assessed at baseline, before the first decision coaching session (after reading the decision aid), after the last decision coaching session and after the final physician encounter in which the treatment decision is made. In the CG, attitude will be assessed before (baseline) and after the physician encounter. The questionnaire comprises the attitude for every option using a four-point Likert scale (“non-sensible” to “sensible”). We will only include the score regarding the treatment option that was finally chosen by patients in the measure of informed choice. The further judgments will be assessed in the scope of the process evaluation. The scale is newly developed.UptakeUptake indicates whether women stick to their decisions made with the medical team (nurses and physicians) within the decision-making process. This information will be extracted from patient records 2 months after the final physician encounter and is included in the measure of informed choice.

To get a dichotomous value for informed choice, we classify women with adequate knowledge and positive attitude toward the chosen option as making an informed choice. Additionally, all sub-dimensions of informed choice (uptake, risk knowledge and attitude) will be analyzed separately. It is possible that diagnosis changes after the decision-making process, for example, if an invasive cancer is detected post-surgery. This changes the preconditions for the treatment decision as well. In such case, the initially favored treatment option (for example, to dispense with radiotherapy) will not be classified as uninformed; instead, the decision will be rated only if the preconditions for the treatment decision (= DCIS) did not change.

##### Decisional conflict

Decisional conflict of patients will be measured using the decisional conflict scale (DCS). Decisional conflict is a condition in which uncertainty about the right decision exists [74]. The DCS includes five subscales: personal uncertainty, modifiable deficits of feeling uninformed, unclear values, inadequate support and perception that an ineffective choice had been made. Sixteen items are scored on a five-point Likert scale (1 = strongly agree to 5 = strongly disagree).

A patient and physician version is available containing the same items (dyadic DCS) [75]. In this study the dyadic version is used and will be supplemented with a nurse version. A German version of the DCS has been validated with 1,286 patients and yielded good test quality [76]. Due to some imprecise item wordings, an adapted physician version will be used that has recently been developed and validated by Kasper et al. but has not been published yet [77, 78].

